##### **Sub-study**

All eligible participants will be scheduled for a sub-study visit in the CHB CTSU for baseline measurements. During the baseline visit, research personnel will obtain informed consent and assent for participation in the sub-study. Once consent/assent is obtained, research personnel will complete baseline measurements under the supervision of the sub-study PI. See Study Measurements and Data Collection for more information.

#### **f. Incentives**

##### **Main Experiment**

Participants will be given a steel water bottle at the end of the baseline visit. Participants will be given a (TBD) at the end of the 12-week visit.

Participants will receive afternoon snacks at every exercise and nutrition education session.

The school will receive (TBD) at the end of the study.

Teachers directly involved in supervising children and contacting parents regarding the study will be compensated for their time.

##### **Sub-study**

Participants will be given a \$50.00 gift certificate to Best Buy and parking voucher or T pass after completing each study visit (baseline and 12-week visits).

## **IV. Study Visits**

### **a. Study Visit Schedule**

#### **Main Experiment (2010)**

| Study Event | Jan | Feb | Mar | Apr | May | Jun | Jul | Aug | Sep | Oct | Nov | Dec |
|-------------|-----|-----|-----|-----|-----|-----|-----|-----|-----|-----|-----|-----|
| Screening   |     | X   |     |     |     | X   |     |     | X   |     |     |     |
| Baseline    |     |     | X   |     |     |     |     |     | X   |     |     |     |

|                    |  |  |  |  |  |   |  |  |  |  |  |   |
|--------------------|--|--|--|--|--|---|--|--|--|--|--|---|
| 12-week assessment |  |  |  |  |  | X |  |  |  |  |  | X |
|--------------------|--|--|--|--|--|---|--|--|--|--|--|---|

#### Sub-study (2010)

| Study Event        | Jan | Feb | Mar | Apr | May | Jun | Jul | Aug | Sep | Oct | Nov | Dec |
|--------------------|-----|-----|-----|-----|-----|-----|-----|-----|-----|-----|-----|-----|
| Baseline           |     |     | X   |     |     |     |     |     | X   |     |     |     |
| 12-week assessment |     |     |     |     |     | X   |     |     |     |     |     | X   |

### b. Intervention Protocol

Following the baseline measurements, participants will be individually randomized into one of the following two treatment conditions: *GoKids* and *Advice-Only*. All participants will receive weekly group nutrition and activity education sessions lasting approximately 30 minutes supported by printed dietary, exercise and motivational advice adapted from existing materials (clinic materials, AHA, CDC and NHLBI materials). The sessions will be taught by UMass student educators trained to deliver a standard message. The *Advice-Only* intervention will consist entirely of these weekly sessions. It was felt to be unethical to offer no support for following a heart-healthy lifestyle to children randomized to the *Advice-Only* condition given the high rate of overweight/obesity and generally poor diet and activity levels in our study population. The *Advice-Only* group will be offered the 12-week GoKids physical activity experience at the close of the trial as an incentive for participation. Children in both groups will receive a small incentive during week 6 and then at the close of the intervention. In addition, classroom and school-wide incentives will be offered, such as healthy lifestyle education sessions for other classes; details will be discussed with the school principal.

The *GoKids* group will receive the GoKids integrated program which uses theory-based behavioral strategies and center-based exercise training. It includes an initial exercise consultation, orientation, and tri-weekly training at *GoKids* Boston. Previous research from GoKids Boston indicates that the energy expenditure from playing interactive video games is comparable to what is expended while walking on a treadmill for the same amount of time. In addition, the use of interactive video games is at a sufficient intensity to engage the participant in MVPA (Bailey et al., 2008). Exercise sessions in the *GoKids* condition will occur 3 times per week lasting 60 minutes each session, for 12-weeks and will include a variety of exercise training activities using the latest interactive exercise games, treadmills, elliptical machines, and strength training equipment located at the UMass facility. All sessions will be supervised by a trained exercise physiologist, with nurse practitioner support available and the classroom teacher present and active with the students.

|                              | Monday
(60 minutes) | Tuesday
(30 minutes)    | Wednesday
(60 minutes) | Thursday      | Friday
(60 minutes) |
|------------------------------|------------------------|----------------------------|---------------------------|---------------|------------------------|
| GoKids (intervention) | Exergaming at GoKids   | Group session in classroom | Exergaming at GoKids      | (no activity) | Exergaming at GoKids   |
| Advice-Only (control) |                        | Group session in classroom |                           | (no activity) |                        |

### c. Randomization Procedures

Staff at the Clinical Research Program (CRP) of CHB will run the randomization software based on the specifications provided by the Principal Investigator (PI). The randomization software (SciRAN) was developed by the Clinical Research Information Technology (CRIT) in collaboration with CRP Biostatistics Core. SciRAN is password protected and access is restricted to designated CRIT and CRP personnel only. The system is designed to a) generate unique and unpredictable random assignments to treatment groups; b) provide users with an audit trail of the process including a verifiable link between subject ID and treatment assignment; and c) provide standard documentation tools.

Key randomization specifications for this pilot study include the following:

- One hundred (100) subjects randomized at CHB, 50 to each of the two treatment arms.
- Children in third through fifth grade will be randomly assigned to one of the following two treatment arms after eligibility is confirmed:
  - Group A:** Nutrition education + exer-gaming sessions
  - Group B:** Nutrition education
- Stratification: normal weight and overweight/obese participants
- The PI will be blind to treatment assignment and block sizes.

Prior to running the randomization program for the study, Dr. [name] confirmed the randomization specifications by completing the Randomization Checklist. [name], Senior CRP Biostatistician, approved the specifications and prescribed the randomization block sizes. Finally, the CRP Data Manager ran the randomization program inputting the approved specification and produced the following randomization documents:

- The Master Randomization Lists: One list per school site: the Master Randomization list includes randomization identifiers, corresponding treatment assignments and randomization blocks.
- The Investigator's Randomization List, which is a 'blinded' version of the Master Randomization List, i.e., absent the treatment assignments and randomization blocks. The investigator's Randomization List will be delivered to the PI.

#### **d. Study Close-out**

Study close-out activities occur at the completion of the study or in the case of early termination. Early termination of the study may occur if funding is stopped or if there are serious adverse events.

Upon completion or early termination of the study, the PI must:

- Confirm the completion of all case report forms
- Review and resolve all data queries
- Fill out and submit a Completion Form to CCI
- Complete a final report

## **V. Study Measurements and Data Collection**

### **a. Administering Surveys/Questionnaires**

#### **Main Experiment**

##### **Enrollment Form**

- Completed by a parent/guardian with other enrollment materials, including informed consent documents
- Includes demographic and medical history that will be entered into study database (date of birth, gender, race/ethnicity, household, health history, healthcare source, employment status, education level, free/reduced price school lunch)

##### **Survey (Diet and Physical Activity)**

- Completed by participant at baseline and 12-week visits

#### Modified Harter Scale

- Completed by participant at baseline and 12-week visits
- See the Appendices for Question-by-Question guidelines

#### Selected TAAG Questions

- Completed by participant at baseline and 12-week visits
- See the Appendices for Question-by-Question guidelines

#### Satisfaction Surveys

- Daily Activity Satisfaction Survey
  - Completed by participant at baseline and 12-week visits
- 12-week Child Satisfaction Survey
  - Completed by participant at 12-week visit
- 12-week Administrator Satisfaction Survey
  - Completed by principal after 12-week visit

### **Sub-study**

#### Dietary Intake Assessment (24-Hour Recall)

- Participants will complete one 24-hour dietary recall interview at baseline and 12-week visits.
- The face-to-face interview will be conducted by the CTSU research dietician using the interactive Nutrient Data System (NDS) (Nutrition Coordinating Center, University of Minnesota, Minneapolis, MN), following standard NDS protocols that have been tested in youth.
- Three-dimensional food models will be used to quantify portion sizes.
- Data will be entered directly into a laptop computer.

### **b. Procedures and Examinations**

Please see the Appendices for the following protocols:

#### **Main Experiment**

- Height, Weight, and Bioelectrical Impedance Assessment (BIA)
- Waist Circumference
- Blood Pressure
- FitnessGram Pacer
- Accelerometry

#### **Sub-study**

- Height and Weight
- EndoPAT (Vascular Reactivity)
- DXA (Body Composition and Density)
- Blood Pressure
- Indirect Calorimetry
- Left Ventricular Mass by Echocardiogram

### **c. Sample Collection**

Please see the Appendices for the following protocols:

#### **Main Experiment**

- Cholestech Total Cholesterol/HDL

#### **Sub-study**

- Fasting Labs
- Urine Pregnancy Test

#### d. Case Report Form Completion

##### Main Experiment

##### Enrollment

| Form                    | Filled out by...  | Recruitment/
Enrollment |
|-------------------------|-------------------|----------------------------|
| Enrollment Form         | Parent            | x                          |
| Liability Agreement     | Parent            | x                          |
| GoKids Facility Consent | Parent            | x                          |
| Medical Release Form    | Parent            | x                          |
| Study Consent Form      | Parent            | x                          |
| Physician's Clearance   | EXCEL Study Staff | x                          |

##### Baseline and 12-week Assessments

| Form # | Form                                   | Completed
by...   | Baseline
Visit (at
GoKids) | Inter-
vention | 12-
week
Visit | As
Needed |
|--------|----------------------------------------|----------------------|----------------------------------|-------------------|----------------------|--------------|
|        | Participation Agreement                | Child                | x                                |                   |                      |              |
|        | GoKids Assent Form                     | Child                | x                                |                   |                      |              |
|        | Study Assent Form                      | Child                | x                                |                   |                      |              |
| 2      | Survey                                 | Child                | x                                |                   | x                    |              |
| 3      | Modified Harter Scale                  | Child                | x                                |                   | x                    |              |
| 4      | Selected TAAG Scales                   | Child                | x                                |                   | x                    |              |
| 5      | Pacer Form                             |                      | X                                |                   | x                    |              |
| 1      | Form 1: Anthropometric
and Lab Data | EXCEL Study
Staff | x                                |                   | x                    |              |
| 6      | Accelerometry                          | Child                | (1 week
after
baseline)    |                   | x                    |              |
|        | Daily Satisfaction
Survey           | Child                |                                  | x                 |                      |              |
|        | 12-week Child
Satisfaction Survey   | Child                |                                  |                   | x                    |              |
|        | Administrator
Satisfaction Survey   | Principal            |                                  |                   | x                    |              |
|        | Attendance                             | Computer
printout | x                                | x                 | x                    |              |
| 7      | Adverse Events
Tracking             | EXCEL Study
Staff |                                  |                   |                      | x            |
| 8      | Trial Termination Form                 | EXCEL Study
Staff |                                  |                   | x                    |              |

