## I. Study Overview

### a. Study Aims and Objectives

#### **Primary Aim:**

To determine the change from baseline in minutes per day spent in moderate or vigorous physical activity (MVPA) as measured by accelerometry. We hypothesize that the *GoKids* intervention will more effectively increase time spent in MVPA compared to baseline vs. the *Advice-Only* condition.

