### c. Timeline

**2010**

| Study Event | Jan | Feb | Mar | Apr | May | Jun | Jul | Aug | Sep | Oct | Nov | Dec |
|-------------|-----|-----|-----|-----|-----|-----|-----|-----|-----|-----|-----|-----|
| Recruitment |     | X   |     |     |     | X   |     |     | X   |     |     |     |
| Consent     |     | X   |     |     |     | X   |     |     | X   |     |     |     |
| Screening   |     | X   |     |     |     | X   |     |     | X   |     |     |     |
| Baseline    |     |     | X   |     |     |     |     |     | X   |     |     |     |
| Randomize   |     |     | X   |     |     |     |     |     | X   |     |     |     |

|                                       |  |  |   |   |   |   |  |  |   |   |   |   |
|---------------------------------------|--|--|---|---|---|---|--|--|---|---|---|---|
| Intervention and Advice-Only sessions |  |  | X | X | X |   |  |  | X | X | X |   |
| 12-week assessment                    |  |  |   |   |   | X |  |  |   |   |   | X |

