#### **e. Baseline Assessment**

##### **Main Experiment**

All participants will be asked to attend GoKids UMass Boston (Boston, MA) for baseline measurements. During the baseline visit, research personnel will screen for eligibility and obtain a comprehensive assessment of baseline cardiovascular, physical activity, and psychosocial measures under the supervision of trained research personnel and exercise physiologists. Non-fasting finger stick total cholesterol (TC) and high-density lipoprotein (HDL) testing will be offered. If no exclusionary criteria become apparent during baseline measurements, participants will be individually randomized to either the center-based exercise intervention (*GoKids*) or an *Advice-Only* condition for 12 weeks, with a follow-up evaluation at 12 weeks after baseline. See Study Measurements and Data Collection for more information.

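### Baseline accelerometry for the primary endpoint is scheduled a week after the baseline visit, and no section shown holds allocation or the first GoKids session until it is done

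*Protocol*

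**What the plan says.** The primary aim (Protocol I.a) is "To determine the change from baseline in minutes per day spent in moderate or vigorous physical activity (MVPA) as measured by accelerometry", compared between GoKids and Advice-Only.

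The passages on the order of events are these:

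- V.d, table of baseline and 12-week assessments: the survey, the Harter and TAAG scales, the Pacer form and the anthropometric and laboratory form are all marked at the baseline visit. Form 6, Accelerometry, alone is entered as "1 week after baseline".
- III.e, Main Experiment: staff are to "obtain a comprehensive assessment of baseline cardiovascular, physical activity, and psychosocial measures" during the baseline visit. Then: "If no exclusionary criteria become apparent during baseline measurements, participants will be individually randomized". The allocated arm is a "condition for 12 weeks, with a follow-up evaluation at 12 weeks after baseline".
- IV.b: "Following the baseline measurements, participants will be individually randomized into one of the following two treatment conditions".
- I.c: baseline and randomization are marked in March and September 2010. The row "Intervention and Advice-Only sessions" begins in those same two months and ends in May and November. The 12-week assessment is marked in June and December.
- IV.c: children are assigned once eligibility is confirmed. Accelerometry is not mentioned.
- III.b, Sub-study: the hospital visit is to be arranged before exercise begins. No matching rule is given for the Main Experiment's accelerometry.

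**The concern.** III.e places the physical activity measure inside the baseline visit and randomization after it. V.d places the accelerometer measure a week later. If children are allocated soon after the visit, as III.e suggests, the value called baseline for the primary endpoint is recorded after randomization, possibly while GoKids children are already exercising.

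Only the GoKids arm has exercise sessions (IV.b), so any session minutes caught by the device raise one arm's baseline and not the other's. The endpoint subtracts that baseline. The error therefore works against the study hypothesis, and the pre-treatment value cannot be recovered once a wave has started.

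**Working it through.** The Protocol states no power, target difference or SD for MVPA, so there is no figure of its own to reproduce. Two checks apply: the calendar and the size of a possible overlap.

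**Calendar**

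Inputs: 12 weeks of sessions = 84 days (IV.b); session months March to May and September to November 2010, assessment in June and December (I.c); follow-up 12 weeks after baseline (III.e).

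- 1 March to 31 May is 92 days. 92 − 84 = 8 days to spare, so sessions must start by 9 March.
- 1 September to 30 November is 91 days. 91 − 84 = 7 days to spare, so sessions must start by 8 September. Recruitment, consent and screening are marked in September too.
- Counting back 84 days from 1 June gives 9 March, and from 1 December gives 8 September. A follow-up exactly 12 weeks after baseline that falls in the assessment month therefore needs a baseline visit no earlier than those dates.

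Taken literally, sessions start on or before 9 March (8 September) and the baseline visit falls on or after the same date. Accelerometry a week after the visit would then fall on or after 16 March (15 September), inside the session period. The grid shows months only and 12 weeks may be approximate, so this shows that the schedule permits overlap, not that overlap will happen.

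**Size of an overlap**

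Inputs: three 60-minute sessions a week (IV.b). Assumptions, because the documents give no figures: a 7-day wear period; the device worn during sessions; session activity added to ordinary activity; a share *f* of session time spent in MVPA, from 25% to 100%.

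Added baseline MVPA per day = sessions overlapped × 60 × *f* / 7.

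| Share *f* | One session | Full week (three sessions) |
|---|---|---|
| 25% | 15/7 = 2.1 min/day | 45/7 = 6.4 min/day |
| 50% | 30/7 = 4.3 min/day | 90/7 = 12.9 min/day |
| 75% | 45/7 = 6.4 min/day | 135/7 = 19.3 min/day |
| 100% | 60/7 = 8.6 min/day | 180/7 = 25.7 min/day |

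If the wear ends before the first session, the addition is 0.

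**Effect on the comparison**

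Write *B* and *F* for mean baseline and follow-up MVPA, with subscripts G and A for the arms. The estimate is (F_G − B_G) − (F_A − B_A). Raising B_G by *c* lowers it by exactly *c*.

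- If the follow-up wear also includes a comparable session week, the session contribution cancels and the estimate moves toward zero.
- If follow-up is worn after sessions have ended, as the June and December marks allow, session minutes count at baseline only and the estimate can fall below zero.
- Adjusting for baseline with slope *b* leaves a bias of −*b* × *c*, because the covariate is then itself affected by treatment. Comparing follow-up values alone avoids the bias but gives up the change-from-baseline endpoint that I.a names.

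**The case against.** The strongest reply is that the Protocol already puts things in the right order. IV.b has randomization follow the baseline measurements, and accelerometry is listed among the Main Experiment procedures (V.b), so a literal reader may take it as one of them. No section says that allocation is made or disclosed on the day of the visit. This stands as far as it goes: IV.b may intend the safe sequence. It does not settle the matter, because III.e ties randomization to what emerges at the visit and runs the 12-week clock from baseline.

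The V.d entry can also be read differently. The table records when forms are completed, so it may mean a week's wear begun at the visit with the form due a week later. That reading is reasonable, but overlap remains possible under it, since nothing shown makes allocation or sessions wait for the wear to end. V.b sends accelerometry to an appendix that is not shown and that could fix the order.

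The calendar can be met. Sessions from Monday 8 March to Friday 28 May would leave 1 to 7 March for the wear. A baseline visit on 1 March, however, puts follow-up 12 weeks later on 24 May, not in June, so not every statement can be kept to the letter. The Sub-study rule also implies some interval before exercise, but its length is not given and it covers only Sub-study children.

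A reader might infer that children are definitely randomized before accelerometry, that overlap is the likely outcome, or that it would cancel the whole treatment effect. The documents do not support these. The order is unclear rather than fixed wrongly, a monthly grid cannot establish likelihood, and with no SD or target difference stated there is no effect against which to measure cancellation. That Advice-Only children would wear the device differently once they knew their arm is conjecture.

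**Conclusion.** The concern holds as an unreconciled sequence for the baseline of the primary endpoint. V.d disagrees with III.e on when physical activity is measured, I.c leaves about 7 to 8 days before sessions must start, and no section shown protects the wear period from allocation or exercise. Followed as written, the schedule allows GoKids session minutes into that arm's baseline.

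If that happens, the difference in change is understated by about 2 to 9 min/day for one overlapping session and about 6 to 26 min/day for a full session week. The upper figure requires all session time to be MVPA. Both ranges rest on the assumed 7-day wear and on sessions adding to ordinary activity. Whether overlap would occur depends on the missing appendix and on how IV.b is meant. The direction, toward or below zero, does not depend on the size chosen.

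**What to change.** State once, and carry through I.c, III.e, IV.b, IV.c and V.d, that the baseline accelerometer wear period is completed and the device collected before allocation is disclosed to the child, family or staff, and before the first session. Reword the Form 6 entry so that it separates the wear dates from the date on which the form is completed, and check that the accelerometry appendix agrees.

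Do not require valid accelerometer data for randomization. That would add an entry condition absent from III.a. Collecting the device is enough to protect the timing.

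The cost is the rewording plus up to about one week between the baseline visit and allocation in each wave. Because the calendar has so little slack, session dates may shift slightly, especially in the September wave, where recruitment, consent and screening share the month. The assessment dates would then need checking against the 12-week follow-up. No additional assessment is needed.

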## **VI. Adverse Event Reporting**

### **a. Risks and Discomforts**

#### **Main Experiment**

Risks and discomforts are expected to be minimal in children enrolled in the Main Experiment, as the intervention will involve physical activity aimed at children. The fingerstick TC and HDL testing will be optional. Minimal risk due to injury may be associated with the exercise intervention, but no more than a school-based physical education class. Questionnaires occasionally can be distressing. Support will be available from GoKids staff experienced in interacting with children.

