### **b. Reporting and Follow-up Procedures**

#### **Main Experiment**

Adverse events associated with the Main Experiment will be immediately reported to the PIs at UMass Boston and CHB. An Adverse Event Tracking Form will be completed and followed up until determined by the PI as resolved or unresolved.

If the event is “reportable”, the Adverse Event Tracking Form will be submitted to the UMass Boston IRB. Reportable adverse events are defined by the UMass IRB as:

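### Main Experiment adverse events are recorded only as they come to notice, while scheduled sessions run 48 to 12 in favour of GoKids, so event counts by arm would not be comparable

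*Protocol*

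**What the plan says.** In the form schedule of section V.d (Baseline and 12-week Assessments), Form 7, "Adverse Events Tracking", is completed by study staff. Its only mark is under As Needed; the baseline, intervention and 12-week columns are empty. In the same table, attendance is marked at all three of those points. The sub-study form for adverse events is also marked only As Needed.

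Section VI.b states: "Adverse events associated with the Main Experiment will be immediately reported to the PIs". It then describes completing the form and following the event up. It gives no question to be put to children and no time at which to put one.

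Section IV.b sets the contact schedule. Both arms have the classroom session: "All participants will receive weekly group nutrition and activity education sessions lasting approximately 30 minutes". For Advice-Only that is all, since the "intervention will consist entirely of these weekly sessions". GoKids exercise sessions "will occur 3 times per week lasting 60 minutes each session, for 12-weeks", and on staffing: "All sessions will be supervised by a trained exercise physiologist, with nurse practitioner support available". The weekly table in that section confirms the pattern: exercise on Monday, Wednesday and Friday for GoKids only, and "Group session in classroom" on Tuesday for both arms.

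Section VI.a describes the injury risk of the exercise programme as minimal, "but no more than a school-based physical education class".

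**The concern.** When nobody is asked about events, an event reaches the form only if someone sees it or a child mentions it. Both chances rise with the number of contacts, and the number of contacts is set by the randomised arm. GoKids children are also watched while they exercise, with clinical support to hand, and Advice-Only children are seen once a week in a classroom. The same injury is therefore likelier to be written down in GoKids.

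A second weakness does not depend on the comparison. Pain that begins at home after a session reaches Form 7 only if the child or family volunteers it. The GoKids count taken alone may thus be incomplete.

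At stake is how any adverse event count from this trial can be read. A surplus in GoKids could be real, or it could come from closer observation, and no later analysis could separate the two, because events that were never elicited cannot be recovered. Section V.e offers no backstop: it schedules monthly review of laboratory parameters and exercise metrics and does not mention adverse events.

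**Working it through.** The protocol states no event rate, capture rate or safety sample size, so it has no figure of its own to reproduce on this point.

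**Step 1: scheduled contacts (section IV.b).**
- GoKids: 3 exercise sessions × 12 weeks + 1 classroom session × 12 weeks = 36 + 12 = 48.
- Advice-Only: 1 × 12 = 12.
- Ratio: 48 / 12 = 4.0.
- Adding the baseline and 12-week visits: 50 / 14 = 3.6.
- Contact time: GoKids (3 × 60 + 30) × 12 / 60 = 42 hours; Advice-Only 30 × 12 / 60 = 6 hours; ratio 7.0.

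**Step 2: effect on recorded events.** Three assumptions are mine and not the protocol's: the true risk is the same in both arms; an event can be noted at any contact in the week in which it occurs; and each contact notes it independently with probability c. Capture is then
- GoKids (4 contacts a week): 1 − (1 − c)⁴
- Advice-Only (1 contact a week): c

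and the recorded ratio is [1 − (1 − c)⁴] / c.

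| c (assumed) | Capture, GoKids | Capture, Advice-Only | Recorded ratio |
|---|---|---|---|
| 0.10 | 0.344 | 0.10 | 3.4 |
| 0.25 | 0.684 | 0.25 | 2.7 |
| 0.50 | 0.938 | 0.50 | 1.9 |
| 0.75 | 0.996 | 0.75 | 1.3 |
| 0.90 | 1.000 | 0.90 | 1.1 |
| 1.00 | 1.000 | 1.00 | 1.0 |

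**Step 3: the same in counts.** Section IV.c randomises 50 children to each arm. With an assumed true risk of 10% in both arms and c = 0.50, the expected recorded events are 50 × 0.10 × 0.938 = 4.7 in GoKids and 50 × 0.10 × 0.50 = 2.5 in Advice-Only. The true expectation is 5 in each.

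**Step 4: with a common question.** If every child is asked the same thing at the 12 classroom sessions and the 12-week visit, solicited contacts are 13 in each arm, a ratio of 1 to 1.

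**The case against.** The strongest reply is that the protocol plans no analysis that this would damage. Neither safety nor injury is an aim or endpoint in section I.a, and no adverse event comparison between arms is described. That stands, and it limits the consequence.

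Several stronger readings are tempting, and the document does not support them.

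- *The risk statement in section VI.a cannot be checked because of Form 7.* Its comparator is a school PE lesson, not Advice-Only. The trial has no PE arm and gives no PE injury rate, so equal recording would still not test it directly.
- *The feasibility aim needs an injury rate.* The feasibility endpoints in section I.a are recruitment, attendance, enjoyment, retention, cost, and barriers and facilitators. Injury is not among them.
- *Reporting only associated events screens out control-arm injuries.* Section VI.b uses parallel wording for the Main Experiment and the Sub-study to send events to different investigators and review boards, and section VIII.c applies it to deviations and complaints as well. It reads at least partly as routing. If staff did take it as a test of relatedness, the imbalance would grow, but the text does not settle this.
- *Those who complete Form 7 meet GoKids children four times as often.* The ratio counts sessions. The protocol does not say which session leaders count as study staff, and teachers paid to supervise children and contact parents (section III.f) may be a further channel.

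It can also be said that As Needed is the usual marking for an event-driven form and does not prove that nobody asks, and that the procedural appendices and Form 7 itself are not in the text available. That is fair. The point is therefore that no scheduled question appears in what is shown, in the form schedule or in the adverse event section.

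**Conclusion.** The concern holds in limited form. Adverse events appear to be collected without a scheduled question, and scheduled sessions differ 48 to 12, so counts by arm would not be comparable. Events are likely to be noticed more often in GoKids, and delayed events in either arm may be missed.

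The size is not known. The range of about 1.0 to 3.4 rests wholly on the assumed capture per contact (1.0 down to 0.10), with equal true risk and independent contacts. A reader might infer that control-arm injuries will certainly be under-recorded, or that a spurious ratio near 4 should be expected. Neither follows: a ratio near 4 needs very low capture at each contact, and the distortion vanishes if capture is nearly complete. Conspicuous or serious events would probably surface in both arms, so minor and delayed ones are the more exposed.

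The primary activity aim is unaffected. This is a low-cost improvement in how data are collected, not a flaw in the trial's main comparison.

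**What to change.** At the weekly classroom session, which both arms attend, ask every child the same one or two questions about injury or illness since the last such session, and ask them again at the 12-week visit. Enter each positive answer on Form 7 whatever the suspected cause, and mark Form 7 in the intervention and 12-week columns of the section V.d schedule as well as under As Needed. Report counts by arm from this common source, and list events seen at exercise sessions separately. An event seen at an exercise session that the child also reports in the classroom stays in the common count, so that the two arms are treated alike.

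The cost is a few minutes at a session that already takes place and a simple tick-sheet, with no added visit or staff. The downside is that more minor, unrelated events will be recorded.
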